## Abstract

**Background:**

Radical radiotherapy, with or without concomitant chemotherapy forms the mainstay of organ preservation approaches in mucosal primary head and neck cancer. Despite technical advances in cancer imaging and radiotherapy administration, a significant proportion of patients fail to achieve a complete response to treatment. For those patients who do achieve a complete response, acute and late toxicities remain a cause of morbidity. A critical need therefore exists for imaging biomarkers which are capable of informing patient selection for both treatment intensification and de-escalation strategies.

**Methods/design:**

A prospective imaging study has been initiated, aiming to recruit patients undergoing radical radiotherapy (RT) or chemoradiotherapy (CRT) for mucosal primary head and neck cancer (MPHNC). Eligible patients are imaged using FDG-PET/CT before treatment, at the end of week 3 of treatment and 12 weeks after treatment completion according to local imaging policy. Functional MRI using diffusion weighted (DWI), blood oxygen level-dependent (BOLD) and dynamic contrast enhanced (DCE) sequences is carried out prior to, during and following treatment. Information regarding treatment outcomes will be collected, as well as physician-scored and patient-reported toxicity.

**Discussion:**

The primary objective is to determine the correlation of functional MRI sequences with tumour response as determined by FDG-PET/CT and clinical findings at 12 weeks post-treatment and with local control at 12 months post-treatment. Secondary objectives include prospective correlation of functional MRI and PET imaging with disease-free survival and overall survival, defining the optimal time points for functional MRI assessment of treatment response, and determining the sensitivity and specificity of functional MRI sequences for assessment of potential residual disease following treatment. If the study is able to successfully characterise tumours based on their functional MRI scan characteristics, this would pave the way for further studies refining treatment approaches based on prognostic and predictive imaging data.

**Trial registration:**

Australian New Zealand Clinical Trials Registry (ANZCTR): ACTRN12616000534482 (26 April 2016).

## Background

Mucosal primary head and neck cancer (MPHNC) has an estimated incidence of over 900,000 cases per year, and is associated with significant mortality, causing more than 350,000 deaths per year[1]. Organ preservation strategies involve the administration of a radical dose of radiation therapy, usually with concomitant chemotherapy, producing 5-year overall survival rates of between 30 and 50% [2]. Despite technical improvements in radiotherapy, significant toxicity may result from these treatments [3, 4].

Prognostication and treatment strategies are informed by clinical features [5] and increasingly by tumour biological features, notably preceding infection with oncogenic strains of human papilloma virus (HPV) [6, 7]. Reliable imaging biomarkers may therefore provide useful data to facilitate adaptive approaches including treatment intensification for poor responders and de-intensification for good responders [8]. Such strategies may improve the therapeutic ratio by reducing dose to organs at risk and increasing dose to areas harbouring subvolumes of more resistant tumour.

Positron-emission tomography using ^18^F–fluorodeoxyglucose (FDG-PET) is currently a standard investigation for initial staging of MPHNC. Retrospective studies have described FDG-PET’s performance in assessing disease following radical radiotherapy [9, 10] and its value in decision-making around surgical salvage has been demonstrated in a prospective trial [11]. Some limitations remain however, with the possibility of false-positive results due to benign tissue inflammation and of false-negative results due to limited spatial resolution.

Magnetic resonance imaging (MRI) has an established role in diagnosis and staging of MPHNC, and its use in radiotherapy planning continues to expand [12]. MRI has superior spatial resolution, better soft tissue definition and does not employ ionising radiation. Furthermore, functional sequences can provide additional information on tissue composition and biology which is not revealed by standard anatomical T1 and T2 weighted scans.

Diffusion-weighted imaging (DWI) characterises tissue based on movement of water within a volume. The diffusivity of water molecules depends on microstructural features of the tissue, such as cellular size and density, and may be quantified with the apparent diffusion coefficient (ADC). Its applications in the upper aerodigestive tract were previously limited by technical factors such as susceptibility artefact from air-tissue interfaces and low signal-to-noise ratio. Modern scanning techniques have been able to overcome many of these issues, and DWI measurements before, during and following RT have been investigated as a diagnostic and prognostic tool [13–18].

Dynamic contrast-enhanced (DCE) MRI provides information on abnormal tumour vasculature, by assessing the travel of gadolinium contrast agent between intravascular and extracellular extravascular space (EES) by means of sequential T1-weighted scans with high temporal resolution. With knowledge of the pre-contrast T1 tissue values, and the concentration-time course of contrast in feeding blood vessels, pharmacokinetic modelling can generate quantitative parameters for analysis of tumour perfusion [19]. These include K^trans^ (the volume transfer constant between blood plasma and EES), K_ep_ (the rate constant between EES and blood plasma) and V_e_ (the fractional volume of EES). The values of these parameters, as well as their distribution in the volume imaged, have been investigated as potential imaging biomarkers both before and after treatment for MPHNC [20–30].

Blood oxygen level–dependent (BOLD) MRI utilises local changes in magnetic susceptibility due to the presence of paramagnetic deoxyhaemoglobin. An increase in deoxyhaemoglobin shortens transverse relaxation time T2*, giving a qualitative indication of tissue hypoxia [31]. The rate of transverse relaxation R2* (1/T2*) can be measured with a multiple-echo gradient echo sequence and has been shown to correlate with tissue hypoxia as measured by polarographic electrodes and immunohistochemistry [32–34]. Pre-clinical and early clinical results suggest that R2* may be a useful biomarker for radiation response and for treatment outcomes [35–37].

Our group completed a pilot study of functional MRI and FDG-PET in a cohort of patients undergoing radical radiotherapy for MPHNC, indicating that carrying out sequential DWI and R2* studies before, during and after radiotherapy was feasible. Initial results, including correlations between imaging studies have been published, while mature data regarding clinical outcomes are awaited [18]. Following this we have initiated a prospective observational study named “MRI in MPHNC”, which aims to gather data on the utility of functional imaging sequences with DWI, DCE and BOLD MRI as biomarkers for prediction and assessment of treatment response.

## Methods

### Study design and consent

This study is a prospective single arm observational trial of patients undergoing curative intent primary radiotherapy, with or without chemotherapy, for MPHNC at Liverpool and Campbelltown Hospitals. Patients are identified and evaluated by the multidisciplinary team. Informed consent is obtained by medically trained personnel as per the trial delegation log. Administrative support, including travel funding for study scans, is provided by clinical trials unit staff.

### Hypotheses

Functional MRI can be used as a reliable imaging biomarker in prediction of treatment response (radiotherapy ± chemotherapy) in MPHNCFunctional MRI can be used as an alternative functional imaging study to FDG-PET scan in assessing response after radiotherapy ± chemotherapyFunctional MRI can differentiate between recurrent or residual malignant disease and post-treatment tissue changes following radiotherapy ± chemotherapy

### Objectives

#### Primary objective

To determine the correlation of pre-, during treatment and post-radiotherapy (± chemotherapy) functional MRI with tumour response at 3 months by FDG-PET scan and with local control at 12 months.

#### Secondary objectives

To prospectively correlate different MRI sequences and FDG-PET findings with disease-free survival (DFS) and overall survival (OS)To determine the best time to perform MRI during radiotherapy treatment for assessing tumour response and local controlTo determine the sensitivity and specificity of functional MRI sequences compared with FDG-PET in assessment of potential residual and recurrent MPHNC following definitive radiotherapyTo assess consistency of image registration, signal information and associated analyses over a relevant time frame in a representative subset of patients

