#### Definition of local control

FDG-PET response at 12 weeks will be defined as a complete metabolic response, partial metabolic response, stable metabolic disease or progressive metabolic disease based on visual assessment by the nuclear medicine physician’s report. Local control for patients will be assessed at 12 months as indicated by having no evidence of local disease on clinical (including endoscopic) examinations and imaging studies at 12 months. Tumour response will be assessed using Response Evaluation Criteria In Solid Tumors (RECIST) criteria version 1.1[39] which is the internationally recognised gold standard assessment method on the evaluation of therapeutic response in solid tumours.

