#### Statistical analysis

Statistical analyses will be performed by using software SPSS and *p* < 0.05 will be considered statistically significant. Chi-square test will be used to compare the prevalence of FDG-PET CMR between MRI-positive and negative groups. Comparisons of the ADC values/maps of pre-, intra- and post-treatment DWI images will be performed by using one way analysis of variance (ANOVA) test. Comparisons of the DCE parameters such as K^trans^, K_ep_, area under the curve (AUC) at initial 60 and 90 s of pre-, intra- and post-treatment will be performed by using the Kruskal-Wallis test. To determine the sensitivity and specificity of DWI and DCE parameters for FDG-PET CMR and 12 month local control, Kappa association statistics will be used. Receiver operator characteristics (ROC) will be used to obtain an optimal threshold for individual MRI parameters.

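### The stated analysis scores MRI, but not FDG-PET, against 12-month local control and plans no paired comparison, so it does not answer how MRI compares with PET

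*Protocol article*

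**What the plan says.** The second hypothesis is that functional MRI could take the place of FDG-PET for assessing response after treatment. The third secondary objective asks for the "sensitivity and specificity of functional MRI sequences compared with FDG-PET in assessment of potential residual and recurrent MPHNC" after treatment.

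The Statistical analysis section gives the method in one sentence: "To determine the sensitivity and specificity of DWI and DCE parameters for FDG-PET CMR and 12 month local control, Kappa association statistics will be used". The only between-group test involving PET makes PET the outcome: "Chi-square test will be used to compare the prevalence of FDG-PET CMR between MRI-positive and negative groups". The only analysis relating PET itself to a later outcome is in the first secondary objective, which correlates MRI and PET findings with disease-free and overall survival.

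The Definition of local control section sets out both references: "FDG-PET response at 12 weeks will be defined as a complete metabolic response, partial metabolic response, stable metabolic disease or progressive metabolic disease", and local control means "no evidence of local disease on clinical (including endoscopic) examinations and imaging studies at 12 months". Under Assessment of MRI sequences, a positive MRI is a good response and a negative MRI a poor one.

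The Background describes PET as a fallible test, "with the possibility of false-positive results due to benign tissue inflammation and of false-negative results due to limited spatial resolution".

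**The concern.** The objective can be read in two ways, and the stated analysis is inadequate for either.

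- **As a comparison of two tests.** Both tests must be scored against one reference for disease. MRI is scored against 12-month local control and PET is not, so there is no PET sensitivity or specificity to set beside MRI's.
- **With PET as the reference.** The result then measures agreement with PET, not detection of disease. Every PET error that MRI avoids is charged to MRI.

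Kappa does not close the gap. It measures agreement between two classifications and does not show which is right when they differ.

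At stake is the basis for any later statement that MRI can substitute for PET. As written, such a statement would rest on agreement with a test that the protocol itself describes as open to error, or on an MRI accuracy figure with no PET figure beside it.

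**Working it through.** **1. The plan's own figure.** The Sample size determination section gives 55 patients for CMR rates of 87% (MRI-positive) and 51% (MRI-negative), with 80% power at the 5% level and allowance for a 40:60 split. For equal groups, two-sided, with pooled variance and no continuity correction:

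n per group = [1.96 × √(2 × 0.69 × 0.31) + 0.842 × √(0.87 × 0.13 + 0.51 × 0.49)]² / (0.36)² = 24.7, rounded up to 25, or 50 in total.

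With 40% MRI-positive the same method gives 21 + 32 = 53. At 55 patients, power is 84.3% (50:50) and 82.0% (40:60). The figure is therefore reproduced to within 2 patients. It covers an association between MRI group and PET CMR, not a comparison of the accuracy of two tests.

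**2. What those design rates imply about agreement with PET.** For MRI-positive share s:

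- CMR = 0.87s + 0.51(1−s)
- sensitivity for CMR = 0.87s / CMR
- specificity = 0.49(1−s) / (1−CMR)

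| s | CMR | Non-CMR of 55 | Sensitivity | Specificity | Kappa |
|---|---|---|---|---|---|
| 40% | 65.4% | 19.0 | 53% | 85% | 0.33 |
| 50% | 69.0% | 17.1 | 63% | 79% | 0.36 |
| 60% | 72.6% | 15.1 | 72% | 72% | 0.38 |

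For s = 50%, observed agreement is 0.435 + 0.245 = 0.68 and chance agreement is 0.50, so kappa = 0.18/0.50 = 0.36. Meeting the design target exactly would still mean only modest agreement with PET.

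**3. How PET error is charged to MRI when CMR is the reference.** The protocol gives neither PET's accuracy nor the residual disease rate, so these are assumptions: residual disease π = 20%, and PET sensitivity (Se) and specificity (Sp) for disease of 85% each. As fractions of all patients:

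- disease, PET non-CMR: 0.20 × 0.85 = 0.17
- disease, PET CMR: 0.20 × 0.15 = 0.03
- no disease, PET non-CMR: 0.80 × 0.15 = 0.12
- no disease, PET CMR: 0.80 × 0.85 = 0.68

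Overall CMR is 0.71, which lies within the 65% to 73% implied in step 2.

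A perfect MRI is positive in every patient without disease and negative in every patient with it. Under the protocol's coding:

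- sensitivity for CMR = (1−π)Sp / [(1−π)Sp + π(1−Se)] = 0.68/0.71 = 96%
- specificity for CMR = πSe / [πSe + (1−π)(1−Sp)] = 0.17/0.29 = 59%
- kappa: observed agreement is 0.68 + 0.17 = 0.85, chance agreement is 0.80 × 0.71 + 0.20 × 0.29 = 0.626, so kappa = 0.224/0.374 = 0.60

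About 0.15 × 55 = 8 patients would be counted as MRI errors although MRI was right in all of them. An MRI that copied PET, mistakes included, would score 100% on both measures.

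**Range.** With residual disease from 15% to 31% and PET sensitivity/specificity from 70%/80% to 90%/90%, the perfect MRI's specificity for CMR runs from 38% to 80%, and its sensitivity from 86% to 98%.

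**4. Can the comparison be made from the planned data?** Yes. MRI at 3 months (Imaging schedule), PET response category at 12 weeks and local status at 12 months (Definition of local control) are all planned in the same patients. Precision will be limited. Assume 8 to 17 local failures among 55 (15% to 31%) and about 80% of failures correctly flagged, which is specificity under the protocol's coding. Exact 95% intervals then run from 35–97% (6 of 8) to 57–96% (14 of 17).

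**The case against.** The strongest reply is that PET is not the only reference. The same sentence also scores DWI and DCE parameters against 12-month local control, which rests on clinical and endoscopic examination as well as imaging. That stands, and it rules out several stronger readings.

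- A reader might infer that MRI can never be shown to be better than PET. This holds only where CMR is the reference.
- A reader might infer that the third hypothesis, on separating residual or recurrent disease from post-treatment change, has no valid analysis. The local-control analysis partly addresses it for DWI and DCE, and it needs no PET comparator.
- A reader might infer that the comparison with PET cannot be made at all. The planned data allow it. It is only missing from the stated analysis.

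Two further replies carry some weight. Relating MRI to 3-month PET response is the declared primary objective and the basis of the sample size, so that analysis is legitimate as agreement or early prediction. And a condensed article may leave a paired test for a secondary objective to a fuller document that is not shown. However, the article does state how sensitivity and specificity will be obtained. It names the references and the statistic, and PET does not appear as a test to be scored. Correlating PET with survival outcomes does not supply PET's sensitivity or specificity.

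**Conclusion.** The point holds in a limited form. The stated analysis scores MRI against PET CMR and against 12-month local control, but it does not score PET against local control and plans no paired comparison. The secondary objective of comparing MRI with FDG-PET, and the hypothesis that MRI could replace it, are therefore not answered by the analysis as stated. Where CMR is the reference, PET's errors count against MRI.

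The 96% and 59% rest on assumed values for residual disease and PET accuracy. They show the direction and possible size of the distortion in the CMR-referenced analysis only and say nothing about the local-control analysis. The absence of a planned PET accuracy analysis and paired comparison is read from the article alone. This is a correction that should be made and is cheap to make. It does not undermine the primary objective.

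**What to change.** Revise the Statistical analysis section as follows.

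1. Score the 3-month MRI (positive or negative) and the 12-week FDG-PET (CMR or not) against 12-month local control as already defined, in the same patients.
2. Report each test's sensitivity and specificity, and the paired MRI-minus-PET difference in each, with 95% confidence intervals. Use McNemar's method separately among patients with and without local control.
3. Base any statement that MRI can replace PET on the intervals for those paired differences.
4. Keep the analysis of MRI against PET CMR, labelled as agreement or early prediction and not as accuracy for disease.
5. State as a limitation that the 12-month reference includes imaging of unspecified type, so its independence from PET is not assured.

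The cost is analysis work and wording, because the scans and outcomes are already planned. The main downside is imprecision: with few local failures the intervals will be wide, and the comparison may not settle whether MRI can replace PET.

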### Endpoints

#### Primary endpoints

Correlation of functional MRI sequences with PET-CT at 3 months following treatment and local control at 12 months, including:Measurement of restricted water diffusion as on DWI, which can be a marker of high cellularity within a tumour, using ADC values, ΔADC and parameter maps of ADC.Measurement of tumour perfusion characteristics from DCE-MRI, using parameter maps and calculated values based on inflow and outflow (K^trans^, K_ep_) as well as degree of contrast enhancement of tissues (Relative Signal Intensity, RSI).Tumour size as defined on anatomical imaging using T2-weighted and/or T1-weighted Volume Interpolated Breathhold Examination (VIBE) Dixon MRI.

#### Secondary endpoints

Correlation of different MRI measurements with 1 and 2 year DFS and OS including:Determination of the ability of DWI for detecting residual or recurrent cancerAssessment of functional MRI in correlation with FDG-PET metabolic response at 3 months and local control at 12 months

### Subject selection

#### Inclusion criteria

18 years or olderHave the ability to give informed consentHistologically-proven invasive mucosal primary squamous cell carcinoma of head and neck region or patients with tumours strongly suspicious for mucosal primary head and neck cancer due to clinical features AND fine needle aspiration (FNA) cytology assessmentPrimary mucosal head and neck cancer (≥T2 and/or ≥N1) AND no evidence of metastatic disease on staging PET/CT or CT (chest ± abdomen ± pelvis)Patient undergoing curative intent primary radiotherapy ± chemotherapy

#### Exclusion criteria

Contraindication to MRI studiesSignificant claustrophobiaPacemaker/implantable defibrillatorImplanted metals e.g. Intraocular clipsKnown allergic reaction to gadolinium (Gd)-DTPA
Previous radiotherapy to the area to be treatedPrimary cancer surgery to the affected areaOther malignancy within 5 years of the current diagnosis, with the exception of successfully treated basal cell or squamous cell skin carcinoma, in situ melanoma, or carcinoma in situ of the cervix

#### Early withdrawal of subjects

If a patient expresses wishes to withdraw from the trial, site staff will explain the importance of maintaining follow-up. A patient may withdraw, or be withdrawn, from the trial for the following reasons:Unacceptable toxicityRequests or requires early discontinuation for any reasonIntercurrent illness which prevents further treatment/follow-upWithdrawal of consent for treatment by patientDevelops, during the course of the study, symptoms or conditions listed in the exclusion criteriaInvestigator discretion

The investigator will also withdraw all subjects from the study if the study is terminated. Subjects are free to withdraw from the study at any time upon their request or the request of their legally acceptable representative.

Patients may re-consent if they change their mind following withdrawal, to resume participation on this trial. The patient will however remain in the trial for the purposes of follow-up and data analysis unless they specifically request otherwise.

### Radiotherapy

All participants will receive standard treatment according to locally agreed protocols [38], based on international evidence-based practice guidelines. This study does not involve a treatment intervention or additional ionising radiation exposure. Therefore, there will not be any additional radiation dose or related side effects by participating in this trial. All imaging performed with ionising radiation is part of standard clinical practice.

### Chemotherapy

All participants will be treated according to locally agreed protocols [38], based on international evidence-based practice guidelines. Therefore, there will not be any additional chemotherapy related side effects by participating in this trial.

### Imaging

#### Imaging schedule

Functional MRI studies are carried out prior to commencing treatment, then weeks 2, 3, 5 and 6 during treatment, followed by 1 month and 3 months post-treatment (Fig. 1).

**Fig. 1 Fig1:**
[figure not shown]
Treatment, imaging and clinical assessment schedule for MRI in MPHNC study

